### 2.2. Study Population

The study sample will include community-dwelling older women aged 60 to 80 years with a clinical diagnosis of UI. The International Consultation on Incontinence Questionnaire—Short Form (ICIQ-SF) [35] will be used to quantify UI symptom severity and impact at baseline and follow-up assessments. UI subtype (stress, urgency, or mixed) will be classified by a specialized physiotherapist according to the diagnostic criteria proposed by the International Continence Society (ICS) [36], based on participant’s medical history, symptom profile, and standardized clinical assessment prior to randomization. Cognitive function will be routinely assessed using the Mini Mental State Examination (MMSE). The Global Deterioration Scale (GDS) will only be used when administration of the MMSE is not feasible or considered inappropriate. When both instruments are available, the MMSE result will determine eligibility. Participants will be recruited from the Nau Gran program at the University of Valencia (Spain) and public centers affiliated with the City Council of Manises (Spain).

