### 2.3. Recruitment Process and Screening

Participants will be recruited through informational sessions, posters, and community outreach activities conducted in collaboration with the Nau Gran program at the University of Valencia and public centers affiliated with the City Council of Manises. Interested individuals will be invited to attend an initial screening visit, during which the study objectives, procedures, potential risks, and benefits will be explained in detail.

The screening process will include demographic data collection, assessment of UI symptoms severity using the ICIQ-SF, cognitive screening using the GDS or MMSE, as appropriate, and a brief health history interview to verify inclusion and exclusion criteria, including the presence of a clinical diagnosis of UI. Only participants meeting all inclusion criteria will be enrolled and randomized. Written informed consent will be obtained prior to enrollment, and participants may withdraw at any time.

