**Figure 7 healthcare-14-02467-f007:**
[figure not shown]
Experimental design. Abbreviations: PMT: power-based multicomponent training; PFM: pelvic floor muscle; PSY: psychoeducational intervention; EX: exercise; i: initial; f: final; s: seconds; min: minutes; CC: contractions; DUR: duration; INT: intensity; REP: repetitions; RPE: rating of perceived exertion; SES: sessions; SET: sets. Note: Component durations are approximate and may vary slightly across sessions. Recovery periods between sets and exercises are included within the planned total session duration of approximately 55–60 min.

**Table 1 healthcare-14-02467-t001:** Inclusion and exclusion criteria.

Inclusion Criteria	Exclusion Criteria
Women aged 60 to 80 years. Community-dwelling (non-institutionalized). Present UI after clinical diagnosis. Ability to walk independently, with or without assistive devices. Functional independence, defined as a Barthel Index score >90. Preserved cognitive function (MMSE score ≥25; GDS score ≥2 only if MMSE cannot be administered). Willingness to participate throughout the intervention and follow-up periods, with written informed consent provided. Not currently engaged in structured physical exercise programs within the previous 3 months Commitment to attend at least 80% of the scheduled intervention sessions.	Previous diagnosis of: (a) neurological disorders (e.g., Parkinson’s disease, stroke, Alzheimer’s disease); (b) severe musculoskeletal conditions limiting physical activity; (c) unstable cardiovascular disease (e.g., unstable angina, NYHA class III-IV heart failure), that could interfere with intervention or assessments. Surgery involving the PF, spine, hip, or knee points within the previous 6 months. Presence of pelvic organ prolapse grade II–IV. Current or recent (<3 months) participation in other structured exercise or intervention programs. Psychiatric or behavioural disorders that may interfere with adherence to the intervention. Ongoing use of medications known to significantly impair neuromuscular or cognitive function (e.g., strong muscle relaxants or sedatives). Inability to understand or follow basic instructions. Visual and/or hearing impairments that may hinder participation in the intervention or assessment.

Abbreviations: GDS: Global Deterioration Scale; MMSE: Mini-Mental State Examination.

**Table 2 healthcare-14-02467-t002:** Multicomponent Exercise Program Schedule.

Program	Weeks 1–2	Weeks 3–7	Weeks 8–12	Weeks 13–18

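### The fallback cognitive criterion in Table 1 (GDS ≥2) runs the wrong way for a deterioration scale: it sets a minimum of deterioration and no maximum

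*Protocol article*

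**What the plan says.** The cognitive inclusion criterion stands in Table 1: "Preserved cognitive function (MMSE score ≥25; GDS score ≥2 only if MMSE cannot be administered". The footnote to that table fixes the meaning of the initials: "GDS: Global Deterioration Scale; MMSE: Mini-Mental State Examination".

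Section 2.2 says when the fallback applies: "The Global Deterioration Scale (GDS) will only be used when administration of the MMSE is not feasible or considered inappropriate". It also gives the order of precedence: "When both instruments are available, the MMSE result will determine eligibility". Section 2.3 mentions "cognitive screening using the GDS or MMSE, as appropriate" without a cut-off or a scoring direction, and makes the criteria binding: "Only participants meeting all inclusion criteria will be enrolled and randomized".

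Other entries in Table 1 bear on the same women. One is "Functional independence, defined as a Barthel Index score >90". Written consent is required. A previous diagnosis of "neurological disorders (e.g., Parkinson’s disease, stroke, Alzheimer’s disease") is an exclusion, as is being unable to understand or follow basic instructions.

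**The concern.** The criterion is meant to select women whose cognition is intact. Its two halves use the same at-least sign on scales that run in opposite directions. For the MMSE the sign demands enough function; for a scale of deterioration it demands enough impairment. Applied literally, the fallback turns away the least deteriorated women and sets no limit on the most deteriorated.

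This matters for three reasons.

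- Entry depends on written informed consent.
- The programme includes standing balance work on unstable surfaces, partly with eyes closed (Table 3), and strength work at RPE 8–9 in weeks 13–18 (Section 2.6.6). Training load is regulated by self-rated exertion.
- The primary endpoint in Section 2.7.1 is a maximal voluntary contraction, which depends on following an instruction. Several secondary outcomes are diaries or questionnaires.

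**Working it through.** There is no figure to reproduce. The check compares the direction of each bound with the direction of its scale, and then looks for any other text that changes the result.

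**Step 1: which instrument.** GDS is expanded as the Global Deterioration Scale in Section 2.2, in the Table 1 footnote and in the abbreviations list. The document therefore leaves no room for another instrument with the same initials.

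**Step 2: scale direction.** The article prints neither the range nor the stage definitions of the GDS. The direction is inferred from the name alone: more on a deterioration scale is worse. The MMSE direction follows from the criterion itself, which treats 25 or more as preserved.

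**Step 3: apply the rule as printed.**

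| Situation | Result on this criterion | Fits the aim of preserved cognition? |
|---|---|---|
| MMSE given, 25 or more | passes | yes |
| MMSE given, below 25 | fails (MMSE decides, Section 2.2) | yes |
| MMSE not given, GDS below 2 | fails | no: this is the least deteriorated end |
| MMSE not given, GDS 2 up to the top of the scale | passes | no upper limit is set |

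**Step 4: look for a correction elsewhere.** Section 2.2 gives the conditions for using the GDS but no cut-off. Section 2.3 gives neither. No section gives an upper limit, a reversed scoring or a second GDS threshold, so Table 1 is the only place where the rule is set. A fault in reading the PDF is unlikely, because the opposite sign survives elsewhere (the significance level in Section 2.8.1 is printed as p ≤ 0.05).

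**Step 5: combine with the other criteria.** All criteria apply jointly, so the others can only remove women.

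- *Impaired end:* the Barthel requirement, consent, the neurological exclusion and the basic-instructions exclusion would remove most severely impaired women. Those who could still pass are mainly women with undiagnosed or milder impairment.
- *Unimpaired end:* a woman failed for a GDS below 2 stays out, because no other criterion can restore her.

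**Step 6: size.** The article does not say how many women will be screened by GDS. Taking 0–5% of the recruitment target as an assumption, 0 × 120 = 0 and 0.05 × 120 = 6, so 0–6 women.

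**The case against.** The strongest reply is that this is a sign slip in a rarely used parenthesis. The MMSE is routine and decides whenever both results exist, so the GDS line may never be used. The intention is plain from the label, and staff would hardly enrol a visibly deteriorated woman as cognitively preserved. Much of this stands: a slip is plausible, the numbers are probably small and may be zero, and the design and analysis do not depend on it. It does not remove the point, because the printed threshold is the only one given and Section 2.3 makes it binding.

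A reader might also infer more than the document supports:

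- **That the trial admits the most impaired women, or has no protection against doing so.** That describes this one line, not entry to the trial. The Barthel threshold, consent, the neurological exclusion and the basic-instructions exclusion all apply as well.
- **That the line contradicts the exclusion of women who cannot follow basic instructions.** It does not. A woman who passes the first and meets the second is excluded, so the exclusion acts as a backstop.
- **That women who cannot be given the MMSE are those most likely to be impaired.** Section 2.2 says only that the test may be infeasible or inappropriate and gives no reasons.

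**Conclusion.** The point holds as an error in a binding eligibility threshold. As printed, the GDS fallback sets a floor on deterioration and no ceiling, against both its own label and the MMSE half of the same criterion.

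The consequence is limited. It reaches only women for whom the MMSE is not used. Among them it wrongly excludes those scoring below 2 and leaves the screening of impairment to the other criteria, which would stop most severe cases. What remains is wrongful exclusion and possible entry of women with undiagnosed or milder impairment, in an unstated number (0–6 under the assumption above). Sample size and planned analyses are unaffected.

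The conclusion rests on two assumptions: that the scale runs in the direction its name implies, and that screening staff apply Table 1 as written.

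**What to change.** Reconcile the direction and the threshold of the GDS criterion in Table 1 with the criterion's label and with the MMSE rule. The clinical team sets the cut-off; none is proposed here. Sections 2.2 and 2.3 state no GDS threshold, so they need only point to the corrected table.

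Section 3.2 requires important changes to eligibility criteria to go to the Ethics Committee for approval before implementation and, where applicable, to be updated in the trial registry. Section 2.1 plans data collection from January 2026 to January 2027, so screening may already have begun. The screening log should be searched for anyone assessed by GDS, whether enrolled or turned away, and those decisions re-checked against the corrected rule.

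The cost is a short wording change, one ethics submission, a possible registry update and a log review. Nothing in the sample size or analysis needs to be redone.

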## Data Availability

No datasets were generated or analyzed during the current study protocol. Data generated during the future randomized controlled trial will be available from the corresponding author upon reasonable request and in accordance with ethical and privacy regulations.

## Abbreviations

The following abbreviations are used in this manuscript:

ABK	Abalakov
ACSM	American College of Sports Medicine
ACT	Acceptance and Commitment Therapy
AE	Adverse Event
AP	Anteroposterior
BIA	Bioelectrical Impedance Analysis
CMJ	Countermovement Jump
CONSORT	Consolidated Standards of Reporting Trials
DMC	Data monitoring Committee
EX	Exercise
EXVERB	Exercise plus Verbal Pelvic Floor Muscle Activation Instructions
EXVERBPSY	Exercise plus Verbal Pelvic Floor Muscle Activation Instructions and Psychoeducation
FES-I	Falls Efficacy Scale International
GDS	Global Deterioration Scale
GLMM	Generalized Linear Mixed Model
HRmax	Maximum Heart Rate
ICIQ-SF	International Consultation on Incontinence Questionnaire-Short Form
iEMG	Intracavitary Electromyography
ITT	Intention-to-Treat
LL	Lower Limb
LMM	Linear Mixed Model
MAR	Missing At Random
MCID	Minimal Clinically Important Difference
MICE	Multiple Imputation by Chained Equations
MMSE	Mini-Mental State Examination
ML	Mediolateral
MTP	Multicomponent Training Program
NYHA	New York Heart Association
PF	Pelvic Floor
PFM	Pelvic Floor Muscle
PMT	Power-based Multicomponent Training
PSY	Psychoeducation/psychoeducational Intervention
RPE	Rating of Perceived Exertion
RSES	Rosenberg Self-Esteem Scale
SAE	Serious Adverse Event
SF-36	36-Item Short Form Health Survey
SPIRIT	Standard Protocol Items: Recommendations for Interventional Trials
TrA	Transversus Abdominis
UI	Urinary Incontinence
4MWT	Four-Meter Walk Test
6MWT	Six-Minute Walk Test
5tSTS	Five Times Sit To Stand
30sSTS	Thirty Seconds Sit To Stand
